### Outcomes and measures

#### Primary study outcomes

The primary outcomes in this study will be the percentage of women that experienced exacerbations during pregnancy (moderate and severe) defined as events for which the participant sought medical attention (i.e. an unscheduled visit to a doctor, presentation to the emergency department room or admission to hospital, or when oral corticosteroids were used for treatment of asthma). Based on previous research undertaken by our research group it is hypothesised that participation in the Antenatal Asthma Management Service will result in a 20% reduction (absolute) in the incidence of asthma exacerbations during pregnancy in the intervention group compared to the control group [28].

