**Methods/design:**

*Design:* Multicentre, randomized controlled trial.

*Inclusion criteria:* Women with physician diagnosed asthma, which is not currently in remission, who are less than 20 weeks gestation with a singleton pregnancy and do not have a chronic medical condition.

*Trial entry and randomization:* Eligible women with asthma, stratified by treatment site, disease severity and parity, will be randomized into either the ‘Standard Care Group’ or the ‘Intervention Group’.

*Study groups:* Both groups will be followed prospectively throughout pregnancy. Women in the ‘Standard Care Group’ will receive routine obstetric care reflecting current clinical practice in Australian hospitals. Women in the ‘Intervention Group’ will receive additional care through the nurse-led Antenatal Asthma Management Service, based in the antenatal outpatient clinic. Women will receive asthma education with a full assessment of their asthma at 18, 24, 30 and 36 weeks gestation. Each antenatal visit will include a 60 min session where asthma management skills are assessed including: medication adherence and knowledge, inhaler device technique, recognition of asthma deterioration and possession of a written asthma action plan. Furthermore, subjects will receive education about asthma control and management skills including trigger avoidance and smoking cessation counseling when appropriate.

*Primary study outcome:* Asthma exacerbations during pregnancy.

*Sample size:* A sample size of 378 women will be sufficient to show an absolute reduction in asthma exacerbations during pregnancy of 20% (alpha 0.05 two-tailed, 90% power, 5% loss to follow-up).

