### Asthma exacerbations during pregnancy are associated with an adverse outcome

Exacerbations are a key feature of asthma and ideal target for improving asthma control and related outcomes. The definition of an asthma exacerbation is any asthma related event that involved one or more of the following; a hospital admission, an unscheduled doctor visit, a course of oral steroids or an increase in medication use. A systematic review identified that 6% of asthmatic women are hospitalized for a severe exacerbation during pregnancy, and that 20% have a severe exacerbation during pregnancy requiring medical intervention [7]. Furthermore, evidence demonstrates that the rates of exacerbations during pregnancy increases according to asthma severity [18]. Among those with mild, moderate and severe asthma the exacerbation rates have been reported as 13%, 26% and 52%, respectively [18]. The corresponding rates of exacerbations leading to hospitalization were 2%, 7% and 27% [18]. Relying solely on asthma severity, however, can be misleading as asthma can worsen during pregnancy regardless of maternal pre-pregnancy severity [7,10]. That is to say; an asthmatic woman can be a mild asthmatic pre-pregnancy and become a severe asthmatic during pregnancy. In addition, the severity of an exacerbation does not always reflect underlying asthma severity (i.e. women with mild asthma can have a severe exacerbation). This means it is difficult to identify accurately those women at risk of worsening asthma during pregnancy.

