As a follow-up to this study a RCT was undertaken to investigate the clinical use of exhaled fraction of nitric oxide (F_E_NO), as a measure of inflammation, to adjust asthma management during pregnancy. Use of F_E_NO to adjust asthma treatment was associated with a significant reduction in the exacerbation rate during pregnancy (0.288 vs. 0.615; p = 0.001) and a reduction in neonatal hospitalizations (8% vs. 17%; p = 0.046) [28]. The major limitation of this trial, however, was that only non-smokers were enrolled in the study as cigarette use inhibits exhaled NO production in asthmatics and therefore can significantly mask the interpretation of NO data [29]. This significantly restricts the generalisability of this approach given the high proportion of asthmatic women who also smoke during pregnancy (reported to be at least 34% in one Australian cohort study) [14]. The applicability of F_E_NO to routine clinical settings is further limited due to issues around expense and accessibility. In addition, as all women in the study attended a respiratory nurse-led asthma management service, this limits the ability to adequately assess the clinical and cost effectiveness of this intervention.

While these two studies demonstrate the feasibility of providing an Asthma Management Service in the antenatal setting and the potential significant benefits it may achieve, an RCT is the only rigorous approach to truly determine the clinical and cost effectiveness of a nurse-led Antenatal Asthma Management Service versus standard clinical care.

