### Sample size

In recognition of potential differences in the implementation and successfulness of the intervention across two distinct treatment sites, the sample size was calculated to ensure adequate statistical power within each treatment site. The total sample size of 378 pregnant women at baseline (189 in each group and each treatment site) was determined by power calculations (using 90% power and a 5% level of significance) using the primary outcomes of difference in exacerbation rate between treatment groups. We considered a 20% decrease (absolute reduction from 45% to 25%) in the incidence of asthma exacerbations as both achievable and clinically significant. The calculated sample size includes an estimated 15% loss to follow-up. We estimate there are at least 360 pregnancies complicated by asthma each year at each hospital and we will need to recruit 27% (n = 95 per site each year) of women presenting to the antenatal clinic per year to complete study recruitment over 2 years.

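### The 20-point planning effect is credited to a trial in which every woman already had nurse-led care, and the 45% control rate has no stated source

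*Protocol article*

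**What the plan says.** Under Primary study outcomes, the protocol article appeals to the group's own previous research and writes that "it is hypothesised that participation in the Antenatal Asthma Management Service will result in a 20% reduction (absolute"). The only citation is reference 28.

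The Sample size section turns this into proportions: "We considered a 20% decrease (absolute reduction from 45% to 25%) in the incidence of asthma exacerbations". It calls the difference achievable and clinically significant, and gives no citation for either percentage. Power is stated "using 90% power and a 5% level of significance" and is said to be adequate within each site.

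The Background section on existing evidence describes reference 28 as a randomized trial of exhaled nitric oxide for adjusting treatment. It reports a "significant reduction in the exacerbation rate during pregnancy (0.288 vs. 0.615; p = 0.001"). It then gives the limitation: "as all women in the study attended a respiratory nurse-led asthma management service", which restricts what can be said about the clinical and cost effectiveness of the intervention. It adds that only non-smokers were enrolled, and concludes that a randomized comparison of the service with standard care is still needed.

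**The concern.** The present trial compares a nurse-led service with standard care, in which women manage their own asthma and seek advice when they need it. No nitric-oxide step is described in either arm. Reference 28 varied the nitric-oxide step and gave the nurse-led service to everyone. Its between-arm difference is therefore not an estimate of the effect of the service, and the Background says as much. The Primary study outcomes section nevertheless uses it as one.

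What is at stake is the meaning of the power claim. A reader takes 90% power to be tied to an effect that earlier work made plausible for this contrast. If that support is missing, a null result could be read as showing that the service does not work, when the assumed effect came from another intervention.

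**Working it through.** **1. The two contrasts side by side.**

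| | Reference 28, as described in the Background | This trial |
|---|---|---|
| What differs between arms | Use of nitric oxide to adjust treatment | Nurse-led service |
| Nurse-led service | All women | Intervention arm only |
| Smokers | Excluded | Not excluded; cessation counselling offered |

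**2. Where the planning pair may come from.** Reference 28 is reported as 0.615 and 0.288 exacerbations per pregnancy. The document does not give the percentage of women affected, so a conversion needs an assumed distribution.

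- Poisson: 1 − exp(−0.615) = 45.9%; 1 − exp(−0.288) = 25.0%.
- Negative binomial, dispersion 1: 1 − 1/(1 + 0.615) = 38%; 1 − 1/(1 + 0.288) = 22%.
- Negative binomial, dispersion 2: 1 − (1 + 2 × 0.615)^(−1/2) = 33%; 1 − (1 + 2 × 0.288)^(−1/2) = 20%.

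The Poisson pair is close to 45% and 25%. With overdispersion the match fails, so this origin is an inference.

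**3. The background rates.** The section on exacerbations and adverse outcome reports that "20% have a severe exacerbation during pregnancy requiring medical intervention", and gives 13%, 26% and 52% for mild, moderate and severe asthma. On the severity rates, a control rate of 45% needs (45 − 26)/(52 − 26) = 73% severe women if the rest are moderate, or (45 − 13)/(52 − 13) = 82% if the rest are mild. Equal thirds give (13 + 26 + 52)/3 = 30%. These rates are not labelled as standard care and may use a different event definition.

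**4. The plan's own figure.** For a two-sided 5% test, "absolute reduction from 45% to 25"%, with 90% power:

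n per arm = [1.960 √(2 × 0.35 × 0.65) + 1.282 √(0.45 × 0.55 + 0.25 × 0.75)]² / 0.20² = 117.4, so 118.

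The total is 236, or 278 with 15% loss (139 per arm). Powered within each of two sites it is 556. Neither is 378, so the power that 378 gives has to be worked out directly.

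**5. Power at 378.** The Sample size section states 15% loss, which leaves 189 × 0.85 = 160.65 per arm pooled and 80.3 per arm within a site.

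Power = Φ{[d √n − 1.960 √(2 p̄(1 − p̄))] / √(p₁(1 − p₁) + p₂(1 − p₂))}

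where d = p₁ − p₂ and p̄ is the mean of p₁ and p₂. For 45% versus 25%:

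- Pooled: (2.535 − 1.322)/0.660 = 1.84, power 97%.
- Per site: (1.792 − 1.322)/0.660 = 0.71, power 76%.

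The abstract states 5% loss instead ("alpha 0.05 two-tailed, 90% power, 5% loss to follow-up"). With 5% loss the figures are 98% and 81%.

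**6. Pooled power over a range, 15% loss.**

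| Control rate | Intervention rate at the planned risk ratio (25/45) | Power |
|---|---|---|
| 20% | 11.1% | 60% |
| 26% | 14.4% | 73% |
| 30% | 16.7% | 81% |
| 45% | 25.0% | 97% |
| 52% | 28.9% | 99% |

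| Drop from 45% | Power |
|---|---|
| 20 points | 97% |
| 17.5 points | 91% |
| 17 points | 89% |
| 15 points | 80% |
| 10 points | 45% |

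**The case against.** Four points can be made for the plan.

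- **The citation is narrow.** Reference 28 is attached to the 20-point hypothesis, not to the 45%/25% pair, and the Sample size section calls the difference clinically significant. This partly stands: a clinically significant difference can serve as a target. It does not support the claim that the effect is expected on the strength of earlier research, and it does not source the 45%.
- **The background rates do not refute 45%.** The 20% covers severe exacerbations, whereas the primary outcome covers moderate and severe events and includes any unscheduled doctor visit. This stands. A reader might infer that the true control rate is near 20%, so that a 20-point drop would mean abolishing almost all exacerbations. The document does not support that.
- **The control rate could be above 45%.** If about 45% was seen with nurse-led care, and the service helps, standard care should do worse. This stands too, which is why the range runs up to 52%, where power is 99%.
- **Pooled power exceeds 90% on the plan's own assumptions.** True. The weakness lies in the basis of the assumptions. The planned incidence rate ratio with its confidence interval will also show what a null result can exclude.

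**Conclusion.** The concern holds in a limited form. The expected effect is credited to a trial that the same document says cannot properly assess the service, and the 45% control rate is unsourced here. The stated 90% power matches neither the pooled figure (about 97%) nor the per-site figure (about 76%) for 45% versus 25% with 15% loss. Pooled, 90% power corresponds to a drop of about 17 to 17.5 points from 45%.

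Two stronger readings are not supported. One is that the 45% and 25% were taken from reference 28: that depends on Poisson counts and is not stated. The other is that 45% is too high and the trial therefore underpowered: the background rates make 45% uncertain, and the error could lie in either direction.

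The power figures assume a pooled-variance comparison of two proportions, which fits the way the Sample size section states the effect, and equal arms. The Poisson regression named for the primary outcome was not modelled.

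**What to change.** - **Primary study outcomes:** remove the attribution to reference 28 and state the 20 points as a target difference judged clinically important.
- **Sample size:** label the 45% as an assumption. Restate the power that 378 women give for 45% versus 25%, pooled and per site, under the stated loss. The 5% in the abstract and the 15% in this section must be reconciled for this.
- **Sample size, table:** add pooled power for control rates of about 20% to 52% at the planned risk ratio, and for 15- and 10-point drops from 45%.

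A check of the blinded event rate at the planned interim is not needed. No action would follow from it, many pregnancies could still be in progress, and a pooled 35% cannot tell 45%/25% from 35%/35%. No increase in sample size is asked for.

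The cost is protocol wording and one table. The drawback is that the stated power becomes less favourable over part of the range.

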#### Secondary study outcomes

For the mother, the secondary outcomes will be:

Asthma related variables defined as; ACQ score and FEV1 throughout gestation, asthma related quality of life, perceived control of asthma, medication adherence and asthma knowledge.

Adverse health outcomes defined as; hypertensive disorders of pregnancy, antepartum haemorrhage, gestational diabetes, preterm labour, need for antenatal hospitalization, weight gain during pregnancy, chorioamnionitis requiring antibiotics during labour, length of postnatal hospital stay, use of postnatal antiobitiocs and postpartum haemorrhage (≥500 mls) and emergency caesarean section.

For the infant/child, the secondary study outcomes will be:

Cases of infant morbidity defined as; Gestational age at delivery (determined by date of the last menstrual period and 18 week ultrasound), Preterm delivery (<37 weeks gestation), birth weight, birth length, head circumference IUGR (defined as those babies whose birth weight was less than or equal to the 5th centile), birth-weight-percentile (calculated using http://www.gestation.net), Apgar scores, congenital malformations, admission to neonatal intensive care unit or special care nursery and stillbirth.

### Sample size

In recognition of potential differences in the implementation and successfulness of the intervention across two distinct treatment sites, the sample size was calculated to ensure adequate statistical power within each treatment site. The total sample size of 378 pregnant women at baseline (189 in each group and each treatment site) was determined by power calculations (using 90% power and a 5% level of significance) using the primary outcomes of difference in exacerbation rate between treatment groups. We considered a 20% decrease (absolute reduction from 45% to 25%) in the incidence of asthma exacerbations as both achievable and clinically significant. The calculated sample size includes an estimated 15% loss to follow-up. We estimate there are at least 360 pregnancies complicated by asthma each year at each hospital and we will need to recruit 27% (n = 95 per site each year) of women presenting to the antenatal clinic per year to complete study recruitment over 2 years.

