### Statistical analysis

Baseline characteristics of all randomized women will be compared descriptively between the study groups. Outcome comparisons will be made according to the treatment allocation at randomization on an ‘intention to treat’ basis. For the primary outcome, the difference in exacerbation rates between groups will be compared using a Poisson regression model. This will enable calculation of the incident rate ratio and associated 95% confidence interval.

For secondary outcomes, discrete outcomes (i.e. low birth weight) will be analysed using log binomial regression and continuous outcomes (i.e. birth weight, gestational age) analysed using linear regression. Continuous variables with repeated measurements (i.e. questionnaire results, ACQ score) will be analysed using a generalized linear mixed model (GLMM) with a random intercept for individuals to account for repeated measurements.

Planned sub-analyses will be undertaken to assess the effects of asthma control, FEV1, asthma medication use, cumulative ICS exposure, asthma knowledge and medication adherence, on the primary and secondary outcomes. SPSS Version 20 (SPSS Inc., Chicago, IL, USA). and Stata IC 11.1 (Stata, College Station, TX, USA) will be used for analyses. Statistical significance will be assessed at the 0.05 level using a two-sided comparative test.

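### The 378 women do not give the power within each site that the plan claims at its own 45% versus 25%, and the plan attaches two different loss rates to the same number

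*Protocol article*

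**What the plan says.** The Sample size section gives the reason for the size: because the intervention may be implemented and succeed differently at the two hospitals, "the sample size was calculated to ensure adequate statistical power within each treatment site". It then gives 378 women at baseline, split as "189 in each group and each treatment site", from a calculation "using 90% power and a 5% level of significance" for an absolute fall from 45% to 25%. It adds: "The calculated sample size includes an estimated 15% loss to follow-up". Recruitment is planned at 95 women per site per year for two years.

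The abstract gives the same 378 and the same 20-point reduction, but with "alpha 0.05 two-tailed, 90% power, 5% loss to follow-up".

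The Statistical analysis section compares exacerbation rates between groups by Poisson regression, giving an incident rate ratio, and adds: "Statistical significance will be assessed at the 0.05 level using a two-sided comparative test". It does not say whether the variance is model-based or robust. The primary outcome, under Primary study outcomes, is the percentage of women with an exacerbation.

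**The concern.** Two things look wrong. First, the abstract and the Sample size section cannot both be right about the loss built into 378. Second, the size is justified by power within each site, yet half of 378 split between two arms leaves fewer than 95 women per arm per site before any loss. That is a small number for detecting 45% versus 25% with high power.

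What is at stake is the description of the design. The Setting section presents the hospitals as a socioeconomic contrast in which the service can be studied in two diverse settings. A reader who believes each site is adequately powered will put more weight on site-specific results than the numbers bear.

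**Working it through.** **Inputs.** From the Sample size section: 378 women in total, 189 per group and 189 per site, 45% versus 25%, 90% power, 5% significance, 15% loss. From the abstract: two-tailed alpha of 0.05 and 5% loss. Two sites and 1:1 allocation give 189/2 = 94.5 per arm per site. The recruitment plan agrees: 95 × 2 = 190 per site. After 5% loss 94.5 × 0.95 = 89.8 remain, and after 15% loss 94.5 × 0.85 = 80.3. The interim analysis is ignored throughout.

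**Methods.** Let z₁ = 1.960, and z₂ = 1.282 for 90% power. The plan does not fix the variance, so three two-sided methods are shown. The evaluable number per arm for 90% power is:

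- A, two proportions with pooled variance: [z₁√(2×0.35×0.65) + z₂√(0.45×0.55 + 0.25×0.75)]² / 0.20² = [1.960×0.6745 + 1.282×0.6595]² / 0.04 = 117.4.
- B, log risk ratio (binary outcome, robust variance): (z₁+z₂)² × (0.55/0.45 + 0.75/0.25) / (ln 1.8)² = 10.507 × 4.222 / 0.3455 = 128.4.
- C, log rate ratio with model-based Poisson variance, treating 0.45 and 0.25 as event rates over one unit of follow-up (an assumption): 10.507 × (1/0.45 + 1/0.25) / 0.3455 = 10.507 × 6.222 / 0.3455 = 189.2.

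**Can the plan's 378 be reproduced?** Totals for 90% power, before rounding up within arms. The whole trial has two arms; the per-site reading has four arm-by-site cells.

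| Method | Whole trial: 0% / 5% / 15% loss | Within each site: 0% / 5% / 15% loss |
|---|---|---|
| A | 235 / 247 / 276 | 470 / 494 / 553 |
| B | 257 / 270 / 302 | 514 / 541 / 604 |
| C | 378 / 398 / 445 | 757 / 797 / 891 |

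No entry with 5% or 15% loss equals 378. Method C matches for the whole trial, but only with no loss allowance.

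**Power that 378 gives.** For A, power is Φ{[0.20√n − 1.960×0.6745]/0.6595}. At n = 80.3 this is Φ{(1.792 − 1.322)/0.6595} = Φ(0.713) = 76%. For B it is Φ{0.5878/√(4.222/n) − 1.960}; at n = 80.3, Φ(0.604) = 73%. For C it is Φ{0.5878/√(6.222/n) − 1.960}; at n = 80.3, Φ(0.152) = 56%.

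| Method | Within one site: 0% / 5% / 15% loss | Whole trial: 0% / 5% / 15% loss |
|---|---|---|
| A | 83% / 81% / 76% | 98% / 98% / 97% |
| B | 79% / 77% / 73% | 98% / 97% / 95% |
| C | 63% / 61% / 56% | 90% / 88% / 85% |

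Other forms of the two-proportion calculation at 15% loss give 71% (continuity correction) to 78% (unpooled variance) per site; an exact chi-square calculation gives 76%.

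**The case against.** **The 90% may refer to the whole trial.** The plan says adequate power within each site and attaches 90%, in the next sentence, to the comparison between groups. So a reader may infer a promise of 90% per site, but the document does not say that in one phrase. This stands, and it limits the charge. It does not rescue the claim: at the plan's own 15% loss, per-site power is below 80% by every two-sided method tried, and the whole-trial reading with either loss rate does not yield 378.

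**The planned analysis is Poisson, so two-proportion figures should not be substituted.** This also stands. Under model-based Poisson variance the whole-trial power is close to the stated 90% (88% at 5% loss, 85% at 15%), so a reader should not infer that pooled power is simply understated. The same model makes the per-site shortfall larger.

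**378 might be an 80% per-site figure.** With 5% loss, method A at 80% gives 88.1 × 4 / 0.95 = 371, or 376 with rounding up in each arm. That is near, but so is the whole-trial Poisson calculation with no loss (189.2 per group). A third route uses the rates 0.615 and 0.288 that the Background reports from the group's earlier nitric oxide trial. Method C then needs 94 per arm per site (376 in total) for 90% with no loss, and 378 would give about 90% per site with no loss and 85% at 15% loss. But the Sample size section states 45% and 25%, not those rates. Where 378 came from is inference.

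**No site-specific test is planned.** True: one overall comparison is described, so calculations about both sites reaching significance, or a null site being read as local failure, answer questions the trial does not pose.

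**The split is not itself an error.** The wording "189 in each group and each treatment site" is most naturally read as marginal totals, as the recruitment rate confirms. Reading it as 189 per arm within each site would require 756 women.

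**Conclusion.** The point holds in this form. The two loss figures contradict each other. At the stated 45% versus 25%, 378 women give per-site power of about 76% for two proportions at 15% loss, with 73% and 56% under two readings of the planned regression. At 5% loss the three figures are 81%, 77% and 61%. None of the two-sided methods tried gives 90% within a site, even with no loss.

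The result rests on equal allocation, equal site sizes, the same effect at both sites, loss that simply reduces numbers, and, for the Poisson figures, one unit of follow-up per woman.

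A reader might go on to infer that the trial as a whole is underpowered. The documents do not support that: whole-trial power at 15% loss is between 85% and 97%, depending on the method. What is wrong is a stated property of the design that the numbers do not deliver.

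**What to change.** Keep 378 and correct the text:

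- Use one loss figure in the abstract and the Sample size section.
- Withdraw the claim that the size ensures adequate power within each site, or replace it with the actual per-site power at the chosen loss.
- Restate whole-trial power under the planned primary analysis and name the method and variance. At 15% loss this is about 97% for two proportions, 95% for a risk ratio with robust variance, or 85% with model-based Poisson variance.
- State that the overall between-group comparison is the powered one and that site-specific results are descriptive.

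The cost is an edit to one paragraph and the abstract, and a less favourable per-site figure in print. No extra women are needed.
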